## Abstract

**Background:**

Intravenous ketorolac is a potent nonopioid analgesic commonly used to treat vigorous pain in children and adults. Despite its widespread use in pediatric emergency settings, ketorolac dosing in children remains “off-label,” with limited high-quality evidence to guide practice. Pharmacokinetic differences between children and adults suggest that lower ceiling doses adopted from adult practice may lead to suboptimal analgesia in pediatric populations. Inconsistent ketorolac dosing practices across centers reflect substantial clinical uncertainty. Amid efforts to reduce opioid use and provide effective nonopioid alternatives, rigorous pediatric trials evaluating ketorolac dosing are urgently needed.

**Objective:**

The primary objective is to determine whether 2 lower-dose intravenous ketorolac strategies (0.25 mg/kg-30 mg or 0.5 mg/kg-10 mg) are noninferior to the standard dosing regimen (0.5 mg/kg-30 mg) in reducing mean pain scores at 60 minutes postadministration in children aged 6-17 years presenting with vigorous pain. The secondary hypothesis is that ketorolac 0.5 mg/kg up to 10 mg will be superior to 0.25 mg/kg up to 30 mg by at least the minimally important difference of 2.0 points on the verbal Numerical Rating Scale (vNRS).

**Methods:**

The KETODOSE trial is a single-center, randomized, double-blind, double-dummy, noninferiority trial conducted at McMaster Children’s Hospital. Eligible participants aged 6 to <18 years with vigorous pain (vNRS >4) are randomized in a 1:1:1 ratio to standard dosing or one of 2 low-dose ketorolac regimens. Study drugs are administered via intravenous push over 5 minutes. Pain scores are assessed at baseline, 30, 60, 90, and 120 minutes. The primary endpoint is the mean change in vNRS score at 60 minutes. Secondary outcomes include pain scores at other time points, time to effective analgesia, rescue analgesia requirements, opioid consumption, and adverse events. Caregiver perceptions regarding analgesic use are evaluated using a mixed-methods semistructured survey. A sample size of 180 participants (60 per group) provides 80% power to detect noninferiority within a margin of 1.0 on the vNRS, assuming an SD of 1.5. Intention-to-treat and per-protocol analyses will be performed.

**Results:**

Recruitment is ongoing. Final analyses will be performed once follow-up is completed for all participants. Results will be disseminated through peer-reviewed publications, conference presentations, caregiver- and clinician-facing educational tools, and national knowledge mobilization networks.

**Conclusions:**

The KETODOSE trial will provide urgently needed evidence to guide ketorolac dosing for acute pain in children. If lower-dose regimens are shown to be noninferior to standard dosing, this may promote safer prescribing practices, reduce adverse events, and support efforts to minimize pediatric opioid use, thereby improving acute pain management in pediatric emergency care.

**Trial Registration:**

ClinicalTrials.gov NCT05641363; https://clinicaltrials.gov/study/NCT05641363

**International Registered Report Identifier (IRRID):**

DERR1-10.2196/76554

## Introduction

### Background

Ketorolac tromethamine is a well-known nonopioid intravenous (IV) analgesic commonly used in children and adults for vigorous pain [1-3]. It is a nonsteroidal anti-inflammatory drug (NSAID) that inhibits the synthesis of inflammatory endogenous substances such as prostaglandins and thromboxanes. Ketorolac has been shown to provide similar analgesia to opioids after outpatient surgical procedures associated with moderate pain, such as fractures, hernia repair, and tonsillectomy [1,4]. Ketorolac is commonly used in the Emergency Department (ED) for renal colic, abdominal pain, chest pain and migraine headaches [5]. However, such use in children is “off-label” as there is a paucity of methodologically sound controlled trials in children to inform optimal and safe dosing.

Previous pharmacological studies show that young children have up to 2- to 4-fold higher clearance and volume of distribution of ketorolac compared to adolescents and adults [6]. This suggests that younger children need a relatively higher dose per kilogram body weight than adults and the currently used 10-15 mg ceiling dose applied to adults may not achieve equivalent analgesia in children [7,8]. Emerging evidence, only applicable to adults, suggests that low-dose ketorolac (10 mg) is as effective as standard dose (30 mg) in acute pain management [5,9-11] with higher doses not conferring further benefit [12]. This has led to clinicians adopting the practice of a 10 mg maximum dose in children without rigorous pediatric evidence. For example, a 10 mg maximum dose in a 50 kg adolescent would equate to 0.2 mg/kg, in contrast to pediatric studies that used 0.5-1 mg/kg, a maximum of 20-30 mg [10,13-16]. In a local survey (February 2022) of our ED physicians, pediatric hospitalists, and surgeons, 10/31 (32%) respondents said that they would administer ketorolac (0.5 mg/kg) up to a maximum of 30 mg, 20/31 (65%) use ketorolac up to a maximum of 10 mg, and 1/31 (3%) did not know the best dose to give. Although the local monograph and order-sets recommend a maximum dose of 30 mg, our local variation in practice is not surprising and reflects clinical uncertainty regarding the optimal dose.

Ketorolac is an excellent alternative to opioids for vigorous pain and it is imperative to conduct pediatric dosing studies to inform both clinicians and regulatory agencies. Given the continued undertreatment of pain in children, its known adverse effects (including prolonged healing times, longer length of stay, less satisfaction) [17], and the lack of high-quality evidence for ketorolac use in children, there is an urgent need for a well-designed, rigorously conducted trial to inform clinical treatment decisions and health care policy. To our knowledge, there are no trials to guide the selection of the most effective and safe ketorolac dose for use in children. This comes at a time when ketorolac, the only available intravenous NSAID in Canada, is being considered increasingly more often to fill the nonopioid gap in treatment for vigorous pain [13,18-21].

### Study Objectives and Hypothesis

#### Primary Objective

In children aged 6-17 years with vigorous pain (as measured on the 11-point verbal Numerical Rating Scale [vNRS]) who are prescribed IV ketorolac by their treating physician, lower-dose IV ketorolac dosing strategies (0.25 mg/kg/dose-30 mg OR 0.5 mg/kg/dose-10 mg) are noninferior to standard dosing (0.5 mg/kg/dose-30 mg) in reducing mean pain scores.

#### Primary Hypothesis

Low-dosing strategies will be noninferior to standard dose by a margin of 1.0 on the 11-point vNRS: (1) ketorolac given at 0.5 mg/kg/dose-10 mg will be noninferior to standard dose ketorolac and (2) ketorolac given at 0.25 mg/kg/dose-30 mg will be noninferior to standard dose ketorolac.

#### Secondary Hypothesis

Dosing at 0.5 mg/kg/dose-10 mg will be superior to 0.25 mg/kg/dose-30 mg by the minimally important difference (MID) of 2.0 on the 11-point vNRS.

#### Secondary Objectives

The objective of this study is to understand patients’ and caregivers’ knowledge, attitudes, perceptions, and emotions on pain, medications, and their use in treating acute pain. As pain is a multidimensional experience, we seek a deeper understanding of participants’ experiences with pain and pain medications by assessing the following domains: (1) caregiver knowledge and attitudes toward widely available analgesics; (2) attitudes and fears associated with IV analgesics; and (3) caregiver perceptions of dosing of analgesics as well as adverse events (AEs) associated with them.

## Methods

### Design

This will be a randomized, noninferiority, double-dummy, quadruple-blinded (participant and their caregiver, clinical staff, research team, outcome assessor, and data analyst), single-center, pediatric ED trial. The study will be conducted using recommendations from the 2010 CONSORT (Consolidated Standards of Reporting Trials) statement extension for noninferiority and equivalence trials [22] (Multimedia Appendix 1).

### Eligibility Criteria

The inclusion and exclusion criteria with their justifications are summarized in Textbox 1.

Inclusion and exclusion criteria with justification.
**Inclusion criteria and justification**
Age 6 years to <18 years: the primary outcome measure (11-point vNRS) is validated for use in children ≥6 years, and no other evidence-based acute pain measure is recommended for younger children [23-25].Currently experiencing vigorous pain (self-reported pain score >4 using the vNRS at the time of enrollment; ketorolac is used to treat moderate to severe pain) [26].Patients seen in the ED or inpatient setting with acute pain ≤30 days in duration [5].Patient with an IV cannula in situ or ordered (to minimize additional pain or distress).
**Exclusion criteria and justification**
Previous enrollment in the trial (to ensure independent observations).Postoperative patients (medically induced pain differs from pathology-related pain).NSAID use within 6 hours or opioid use within 4 hours, or both, before recruitment (to avoid overdosing and confounding).Actively followed and treated by the chronic pain team (response to analgesics may be altered).Cognitive impairment in the caregiver or child (inability to respond to study questions).History of gastrointestinal bleed or ulcers, inflammatory bowel disease, coagulation disorders, cerebrovascular bleeding, or known arterio-vascular malformations (increased bleeding risk).History of chronic and active renal disease (excluding renal calculi and urinary tract infections).History of chronic and active hepatocellular disease (ketorolac is metabolized in the liver).Known pregnancy at the time of enrollment (risk of closure of the patent ductus arteriosus in the fetus).Known hypersensitivity to NSAIDs or opioids.Inability to obtain consent (language barrier without availability of a translator).

### Interventions

To maintain blinding of bedside clinical staff, patients, and research staff, we will administer an active intervention (ketorolac) and 2 controls (identical normal saline placebo) to each patient at 3 differing doses.

1) Standard-dose group A: IV ketorolac 0.5 mg/kg to a maximum of 30 mg, IV normal saline placebo given at 0.25 mg/kg to a maximum of 30 mg, or IV normal saline placebo given at 0.5 mg/kg to a maximum of 10 mg.

2) Low-dose group B. Group B1: IV ketorolac 0.5 mg/kg to a maximum of 10 mg, IV normal saline placebo given at 0.25 mg/kg to a maximum of 30 mg, or IV normal saline placebo given at 0.5 mg/kg to a maximum of 30 mg. Group B2: IV ketorolac 0.25 mg/kg to a maximum of 30 mg, IV normal saline placebo given at 0.5 mg/kg to a maximum of 30 mg, or IV normal saline placebo given at 0.5 mg/kg to a maximum of 10 mg.

For rescue analgesic therapy, any participant can be given any other non-NSAID analgesic at the discretion of the treating physician at least 60 minutes after the trial medication is administered. To minimize overdosing or AEs, any other NSAIDs can be given 6 hours post-intervention.

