### Methods to Protect from Bias

Our study drug kits will contain active ketorolac and normal saline placebo (labelled as ketorolac) with instructions on dosing as per the randomization schedule. Ketorolac is identical to a normal saline placebo in appearance, consistency, and smell. Vials will contain clear liquid ketorolac 30 mg/ml or normal saline placebo ketorolac 30 mg/ml. Vials will be stored in consecutively numbered study drug kits according to the randomization schedule generated by the McMaster Children’s Hospital research pharmacy. The double-dummy design will ensure blinding of the research nurse drawing up and administering the drug. Bedside physicians and nurses, participants, and their families, investigators, research nurses, and clinical research assistants will all be masked to prevent bias in trial procedures and outcome assessment. Once participants are randomized, we will restrict all other pharmacologic analgesic cointerventions except acetaminophen and rescue therapy. Unblinding will not be permitted under any circumstances, as all participants will receive ketorolac and knowledge of the specific dose would not alter clinical management. Other medications that may be part of the patient’s treatment plan, such as antiemetics, antibiotics, or antihistamines, can be coadministered. Because the primary outcome is based on a self-reported pain scale, the semistructured survey will be conducted only after outcome assessments are completed. Research assistants can complete the semistructured survey after the 6-hour outcome assessment or, if the patient is discharged, within 7 days by phone or electronically. The trial is registered on clinicaltrials.gov (NCT05641363) [30].

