### Concomitant Medications

To decrease the confounding effects of other analgesics, we will exclude anyone who, before randomization, received any NSAIDs or opioids in the preceding 6 hours and 4 hours, respectively. We will not allow any other concomitant analgesics (except acetaminophen) administration during the study enrollment (from randomization-60 minutes postrescue therapy if it was required). Patients who have taken acetaminophen before randomization will be eligible to participate. Acetaminophen is widely available for use as an over-the-counter medication analgesic and is effective for mild pain but not for moderate or severe pain. Ketorolac should still be effective when given alongside acetaminophen and has a different mechanism of action. In addition, patients with migraine will be allowed to have coadministration of antiemetics such as metoclopramide or ondansetron. This should not affect our outcomes since all those participants will receive ketorolac (at differing doses) as the only analgesic. All cointerventions will be recorded.

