#### Secondary Endpoints

Secondary endpoints include the following:

vNRS score at 30, 90, and 120 minutes as well as 6 hours post administration.Proportion of participants who achieve the 2-point vNRS MID pain score reduction at 60 and 120 minutes.Proportion of participants who change the severity of their baseline pain category at all time points (mild = 0 to 3, moderate = 4 to 6, severe ≥7 on the vNRS)[24].Time to effective analgesia (ie, time at which a vNRS <3 is achieved postintervention).Proportion of participants requiring any rescue analgesia in each trial arm.Total amount administered as measured by morphine equivalent mg/kg within 8 hours of intervention.

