### Analysis Plan

#### (A) Primary Objective Analysis Plan

Data will be described in terms of mean (SD) or 95% confidence limits for normally distributed data and frequency (percentage) in the case of categorical data. The primary endpoint is the difference between the mean reduction in pain scores between each of the low-dose groups (B1, B2) and the standard-dose group (A) 60 minutes post intervention. The primary analysis will include all participants randomized based on the intention to treat analysis and a sensitivity per-protocol analysis will also be performed. A priori, the primary analysis will be adjusted for baseline pain scores using the analysis of covariance (ANCOVA)*.* Generalized estimating equations will be used to examine the impact of baseline pain score on vNRS outcomes across the entire time frame. Noninferiority would be shown if the lower limit of the 95% CI for the between group (groups B1vs A or B2 vs A) differences in the primary endpoint is >1.0. If >5% [34] of our vNRS scores are missing within 120 minutes, we will use multiple imputation to create 5 datasets wherein any missing pain data will be imputed with the Markov chain Monte Carlo method. For secondary endpoints, we will describe those outcomes using descriptive statistics and perform a linear (continuous), logistic, or ordinal regression (categorical or ordinal). If both low-dose strategies are shown to be noninferior to standard dose, we will conduct an exploratory analysis to see if one low-dosing strategy is superior to the other (group B1 vs B2). This will be conducted using ANCOVA to adjust for baseline pain scores and superiority will be determined by a difference that is defined by the MID of 2.0 on the 11-point vNRS. All analyses will be conducted in a blinded fashion. The research pharmacist will provide the trial statistician with anonymized group allocation codes, without revealing the dosing strategies associated with each group. The group identities will remain blinded to the statistician until the first draft of the manuscript with results has been completed. All analyses will be done using SAS (version 9.4; SAS Inc).

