**Secondary outcomes**											
		**Efficacy**									
			Pain relief at all time points		Between group differences in pain score at all study time points at 30, 90 and120 minutes		Low dose will be noninferior to standard dose at all time points.		GEE^e^: adjusted for baseline pain scores		
			Pain relief by the MID		Proportion who achieves a 2-point vNRS reduction at 60 and 120 minutes		Low dose will be noninferior to standard dose ketorolac regimens in reducing pain by the 2-point MID^f^ on vNRS		Regression analysis		
			Pain category change		Proportion of participants who change their baseline pain category at all time points (mild 1 to 3, moderate 4 to 6, severe ≥7 on vNRS)		No difference between low dose and standard dose ketorolac in pain category change at all time points		Regression analysis		
			Time to achieve mild or no pain level		Time to effective analgesia as measured by the time when vNRS of <3 is achieved		No difference between all ketorolac dosing arms.		Cox regression analysis		
			Rescue analgesia		Proportion of participants requiring any additional analgesia in each trial arm		No difference between all ketorolac dosing arms		Regression analysis		
			Opioid sparring		Total amount of opioid administered within 8 hours of intervention		No difference between all ketorolac dosing arms		Regression analysis		

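### Relief from rescue analgesia given after 60 minutes counts for the study dose in the later secondary endpoints, and can mask inferiority of a low dose if rescue differs between arms

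*Protocol article*

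**What the plan says.** **Rescue.** Under Interventions, any participant may receive "any other non-NSAID analgesic at the discretion of the treating physician at least 60 minutes after the trial medication is administered". This includes opioids. Methods to Protect from Bias exempts rescue from the limits on other analgesics: "we will restrict all other pharmacologic analgesic cointerventions except acetaminophen and rescue therapy". Concomitant Medications bars other analgesics except acetaminophen but provides for rescue if it is needed.

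**Later endpoints.** Secondary Endpoints lists "vNRS score at 30, 90, and 120 minutes as well as 6 hours post administration", the 2-point responder proportion at 60 and 120 minutes, change of pain category at all time points, and "Time to effective analgesia (ie, time at which a vNRS <3 is achieved postintervention".

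**Hypotheses and models in Table 1.**
- Scores at 30, 90 and 120 minutes: "Low dose will be noninferior to standard dose at all time points", by GEE "adjusted for baseline pain scores". The 6-hour score is not in this row.
- 2-point responders at 60 and 120 minutes: noninferiority, by regression.
- Category change: no difference, by regression.
- Time to vNRS <3: no difference, by Cox regression.

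**What deals with rescue.** The proportion rescued and the opioid amount within 8 hours are separate secondary endpoints. No section says how a score or event after rescue enters the other endpoints. The imputation rule in the Analysis Plan covers missing scores only, and Table 1 limits the per-protocol sensitivity analysis to the primary and safety outcomes.

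**The concern.** A child whose study dose fails, who is given an opioid after 60 minutes and who then reports a low score at 120 minutes adds a low score to the assigned arm. The same child can count as a 2-point responder, as having moved to a milder category and as having reached effective analgesia. If a low dose is weaker, more of its children are likely to be rescued, and the later differences move toward zero. Under a noninferiority hypothesis, and under one of no difference, that movement favours the hypothesis.

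The later times matter here. Rationale for Treatment Dose puts the maximum effect of ketorolac at 2 hours, and the section on advisor involvement records that 2 hours was the primary time point first planned. A dose difference might therefore be most visible at the times when rescue is allowed. The protocol also treats other analgesics as confounders when it sets eligibility, but states no matching rule for scores after 60 minutes.

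**Working it through.** **The plan's own figure.** Inputs from Sample Size Calculations: margin 1.0, SD 1.5, expected difference 0.2, one-sided alpha 0.025, power 80%.
- Normal approximation: n = 2 × 1.5² × (1.96 + 0.842)² / (1.0 − 0.2)² ≈ 55.2, so 56 per group.
- Noncentral t: power is 79.9% at 56 and 80.6% at 57, so 57 per group (171 in total), as stated.
- Allowing for 5% withdrawal: 57 / 0.95 = 60 per group, as stated.

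The sample size reproduces, and this point does not touch it.

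**Illustration at 90 or 120 minutes.** The article states no margin or confidence-interval rule for these times, so the primary values are borrowed. It gives no rescue rates or effects, so those are assumed.
- D is the true difference without rescue (low minus standard; positive means the low dose is worse).
- p_low and p_std are the proportions rescued, and R is the mean fall in vNRS from rescue.
- Bias b = R × (p_low − p_std), and the observed difference is D − b.
- SE = 1.5 × √(2/60) = 0.274.
- P(noninferiority declared) = Φ((1.0 − D + b)/0.274 − 1.96).

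At D = 1.0 the rate should be Φ(−1.96) = 2.5%.

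| Extra rescue in low-dose arm | R | b | Observed difference | False noninferiority |
|---|---|---|---|---|
| 0 | any | 0 | 1.00 | 2.5% |
| 10 points | 2 | 0.20 | 0.80 | 10.9% |
| 10 points | 3 | 0.30 | 0.70 | 19.4% |
| 15 points | 3 | 0.45 | 0.55 | 37.6% |
| 20 points | 2 | 0.40 | 0.60 | 30.9% |
| 20 points | 3 | 0.60 | 0.40 | 59.1% |

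**Simulation check.** The formula treats rescue as unrelated to the child's pain. In 5,000 simulated trials, rescue was instead given with probability 0.7 when the 60-minute score was 5 or more. Further assumptions were a standard-arm mean of 4.0, SD 1.5 and a correlation of 0.7 between the 60- and 120-minute scores. At D = 1.0 about 18% and 35% were rescued, and false noninferiority was 10.1%, 28.6% and 45.8% for R = 1, 2 and 3. At D = 1.5 it was 0.2%, 3.1% and 17.3%.

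**Endpoints without a margin.** For the responder, category and time endpoints the check is one of definition. Each is met by a score reached after the intervention, and none is conditioned on being free of rescue, so relief after rescue satisfies it.

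**The case against.** **Silence is not a decision.** The article never says that scores will be analysed as recorded regardless of rescue. It is a condensed account, and the analysis plan, which is not at hand, may settle the matter. This stands as a caution. But the article does fix the hypotheses, the model with its single covariate and the event definitions, and followed as written these count relief after rescue.

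**As-observed scores can be legitimate.** A comparison regardless of rescue is a valid treatment-policy comparison when it is declared and read beside rescue use. Rescue and opioid use are reported by arm, so an imbalance would be visible. This stands, and is why the as-observed analysis should be kept. Visibility alone does not correct a noninferiority statement.

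**The figures are assumed.** Rescue need not be an opioid, so an effect of 2 to 3 points is not assured. The plan expects a true difference of 0.2, not 1.0. The error rates are therefore illustrations, not forecasts.

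**Stronger readings that the document does not support.** A reader might infer that:
- noninferiority is claimed for time to analgesia or category change. Table 1 gives both a hypothesis of no difference.
- the 1.0 margin and confidence-interval rule govern the later scores. They are stated only for the primary endpoint.
- inferiority is necessarily hidden. That requires rescue that is both unequal and effective.
- the primary result is compromised. Rescue is allowed only from 60 minutes, when the primary score is taken.

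**The obvious repair is debatable.** Carrying the last score before rescue forward would often repeat the 60-minute value, although the stated peak is at 2 hours. Rescue is also discretionary, with no pain threshold, so counting every rescued child as a failure may misclassify some. Neither rule should therefore be the only analysis of the scores.

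**Conclusion.** The concern holds for secondary endpoints. As defined, the noninferiority comparisons of scores at 90 and 120 minutes and of 2-point responders at 120 minutes, and the no-difference comparisons of category change after 60 minutes and time to vNRS <3, credit relief after rescue to the study dose. If a low-dose arm is rescued more often and rescue works, this can mask inferiority.

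With 10 to 15 points more rescue and an effect of 2 to 3 points, the difference shrinks by 0.20 to 0.45. False noninferiority at a true difference of 1.0 then rises from 2.5% to about 11% to 38%. This rests on the borrowed margin, SD and group size and on assumed rescue figures; with equal rescue the rate stays at 2.5%. The primary endpoint is largely protected and the sample size is unaffected. The analysis should be changed, but the trial's main conclusion does not depend on it.

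**What to change.** Change the analysis wording before the group codes are broken. No change to the clinical rescue rule is proposed.

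1. **Responders and categories.** Count a child rescued before the assessment as a non-responder for the 120-minute 2-point endpoint, and as not improved for category change after 60 minutes.
2. **Time to vNRS <3.** Treat rescue before the event as not achieving effective analgesia, either by censoring at the end of follow-up or as a competing event. Do not censor at the time of rescue.
3. **Scores at 90 and 120 minutes.** Report a rescue-adjusted (composite) analysis, with its scoring rule fixed in advance, beside the as-observed GEE. Claim noninferiority at those times only if both agree, and show the proportion rescued by arm next to them.
4. **Data.** Confirm that the time of rescue is captured. The article says that cointerventions are recorded and other analgesia is abstracted from charts, but does not mention timing.

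The cost is a few lines of text, one further analysis and possibly some chart abstraction. The secondary results may be less favourable and describe usual care with rescue less directly, but the as-observed analysis keeps that view.
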